#### Planned subgroup analysis

Analyses will be conducted so as to assess for the role of self-esteem mediating any observed change in levels of depression within the treatment group. Also, self-esteem and depression will be assessed as potential mediators of change within the severity of psychotic symptoms within the treatment group.

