## Design

A rater-blind randomised controlled trial using intention to treat comparing positive memory training (PoMeT) and treatment as usual (TAU) with TAU alone. The intervention is to be completed within 3-months from the date of randomisation. Assessments are conducted at baseline, 3-months, 6-months and 9-months from randomisation as shown in Figure 1.

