Costs will be assessed from a broad societal perspective using an amended version of the Client Service Receipt Inventory [28] and therapists’ records. These will include information on all PoMET treatment related costs, other health care resource use costs (including in-patient stays, outpatient visits, community mental health service contacts, primary care contacts, and medications), social care costs, and broader societal impacts (including costs to the patients and their families and lost productivity costs). Costs will be calculated using UK national-level unit costs.

Assessments will be conducted at baseline, 3-months (end of treatment) and at 6-months and 9-months after randomisation. All measures will be completed at baseline, 3-month and 9-month assessment. The 6-month assessment includes only measures of depression, patient health status (including quality of life and wellbeing) and costs.

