### Analysis

#### Power

A sample of 50 per group will have 80% power to detect the PoMeT + TAU group presenting with a BDI-II score of 7 or more lower than the TAU group at the 2.5% level of significance (two-tailed).

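### Both mediation analyses are set within the PoMeT arm alone, where no indirect effect of the randomised treatment can be estimated

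*Protocol article*

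**What the plan says.** In the protocol article, the section headed "Planned subgroup analysis" contains two mediation analyses. The first concerns "the role of self-esteem mediating any observed change in levels of depression within the treatment group". The second says that "self-esteem and depression will be assessed as potential mediators of change within the severity of psychotic symptoms within the treatment group". Neither sentence names a contrast with TAU, a model or a significance level.

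The Design section describes a randomised trial "comparing positive memory training (PoMeT) and treatment as usual (TAU) with TAU alone". The Planned analysis section compares outcome measures between the two arms by linear mixed-effects models, but does not bring group membership into the mediation analyses. On the visit schedule, Secondary outcome measures says: "All measures will be completed at baseline, 3-month and 9-month assessment". That statement is not limited to one arm.

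**The concern.** A mediation analysis in a randomised trial asks how much of the effect of allocation on the outcome runs through the mediator. It needs the path from allocation to mediator, and the path from mediator to outcome with allocation held fixed. Inside the PoMeT arm allocation is a constant. The first path cannot be estimated there, and so neither can an indirect effect of PoMeT.

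What can be estimated is an association between changes in self-esteem and depression, or between either of these and change in psychotic symptoms. Such an association can exist without any contribution from PoMeT. The Treatment as usual section allows medication and other psychosocial interventions alongside PoMeT. Entry requires a BDI-II of 14 or more, so some fall in depression is expected in both arms. Only the TAU arm can separate these sources from PoMeT, and the stated analysis set leaves it out.

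At stake is the explanation of any benefit. The Background cites an earlier study in which self-esteem appeared to mediate the reduction in depression, and this section is the only stated test of that pathway here.

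**Working it through.** **The plan's own figure.** No figure is given for mediation. The only one is in the Power section: "A sample of 50 per group will have 80% power to detect the PoMeT + TAU group presenting with a BDI-II score of 7" points or more, at a two-sided 2.5% level. No standard deviation is stated, so it cannot be reproduced, only inverted: SD = 7 / [√(2/50) × (2.241 + 0.842)] = 7 / (0.2 × 3.083) = 11.35. That is plausible. It matters here only because it sets 50 patients in the PoMeT arm.

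**Inputs.** From the article: 50 per arm. Assumed: a true PoMeT effect of zero; a 5% two-sided level for mediation; a correlation r (absolute value) of 0.1 to 0.6 between change in mediator and change in outcome; a natural change of 0, 0.3 or 0.5 SD, the same in both arms.

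**Analytic check of the change-on-change test in one arm.** By the Fisher z approximation, the probability of significance is Φ(atanh(r) × √(n − 3) − 1.96). With n = 50, √47 = 6.856:

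- r = 0.1: Φ(0.688 − 1.96) = 10.2%
- r = 0.2: Φ(1.390 − 1.96) = 28.4%
- r = 0.3: Φ(2.122 − 1.96) = 56.4%
- r = 0.4: Φ(2.904 − 1.96) = 82.8%
- r = 0.5: Φ(3.766 − 1.96) = 96.5%

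The probability passes 50% where atanh(r) = 1.96 / 6.856 = 0.286, that is r of about 0.28. With 40 patients the figures are 47% at r = 0.3 and 73% at r = 0.4.

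**Simulation.** There were 4,000 trials per scenario and three analyses:

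- A: change in outcome regressed on change in mediator, PoMeT arm only.
- B: pre-post product test, PoMeT arm only; mean change in the mediator and the mediator-outcome slope must both be significant.
- C: two-arm joint test; group to mediator, and mediator to outcome given group, must both be significant.

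Percentage of trials reporting mediation when PoMeT does nothing (ranges for A and C are over the three levels of natural change):

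| r | A | B, no natural change | B, 0.3 SD | B, 0.5 SD | C |
|---|---|---|---|---|---|
| 0.1 | 10.6-11.7 | 0.5 | 5.7 | 11.0 | 0.7-0.8 |
| 0.2 | 28.4-30.8 | 1.4 | 15.5 | 26.1 | 2.4-2.8 |
| 0.3 | 56.4-58.5 | 2.8 | 31.2 | 54.9 | 3.8-4.2 |
| 0.4 | 82.8-83.0 | 3.6 | 43.2 | 77.5 | 4.2-5.2 |
| 0.5 | 96.6-96.8 | 4.9 | 53.6 | 90.7 | 4.8-5.5 |
| 0.6 | 99.7-99.8 | 4.8 | 54.1 | 92.4 | 4.5-5.4 |

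A and C are not like for like, since A tests one path and C two. B against C is the fairer comparison: both require two paths, and they differ in whether the first is a before-after change or a randomised contrast. B exceeds C once there is natural change, and does not when there is none.

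Regression to the mean works differently in the two within-arm tests. It shifts mean change, which feeds B. It does not by itself create the correlation that A detects; that needs fluctuation shared between the two measures.

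**The case against.** Four points can be made on the other side.

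- **The wording may be looser than it looks.** The restriction could describe the change to be explained, namely that seen in treated patients relative to TAU, instead of the analysis set. The article uses the word within loosely elsewhere, and mediation is not a subgroup analysis on any reading. This is possible. The heading and the repeated phrase favour the restricted reading, and if the looser one was meant the text still needs correcting.
- **A reader might infer that the analysis will usually report mediation even if PoMeT does nothing.** The documents do not support that. They state neither the test nor the correlation. The rate is about 11% at r = 0.1 and 28-31% at r = 0.2 for change on change, and at most 5% for a pre-post product test without natural change.
- **A reader might also infer that the mechanism would be supported whether or not PoMeT works.** That goes too far. Self-esteem is a listed outcome, and the mixed models in Planned analysis estimate the effect of allocation on self-esteem and on BDI-II. An ineffective PoMeT would usually show no difference on either, and a within-arm association would be read beside those results. They do not, however, supply an indirect effect.
- **The order in time of mediator and outcome is not specified.** A journal article commonly leaves that to the analysis plan, and the visit schedule allows a 3-month mediator with a later outcome. It is no finding.

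What stands is that, on the literal reading, the stated analysis set cannot answer the mediation question at any correlation.

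**Conclusion.** The concern holds for the single-arm restriction in both sentences. With allocation constant, neither the path from PoMeT to the mediator nor an indirect effect can be estimated, and a PoMeT mechanism cannot be told apart from change that also occurs under TAU. This follows from the design and needs no assumed number.

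How often it would mislead does rest on assumptions. With no PoMeT effect, a change-on-change test in 50 treated patients can be significant, and with a correlation of about 0.3 or more often will be. A pre-post product test misleads only to the extent that patients change naturally.

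Severity is moderate. Mediation is not among the primary or secondary hypotheses, and the primary BDI-II comparison, the power statement and the economic evaluation are untouched.

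**What to change.** In both sentences, replace the restriction to the treatment group with a mediation analysis in all randomised participants:

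- exposure: randomised group;
- mediator: the 3-month value (self-esteem for depression; self-esteem and depression for psychotic symptoms);
- outcome: the 9-month value;
- covariates: baseline mediator and baseline outcome;
- report: the indirect effect with a confidence interval, and an explicit statement of the assumption of no unmeasured mediator-outcome confounding, which randomisation does not secure.

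Nine months serves both analyses. The article says that "The 6-month assessment includes only measures of depression, patient health status (including quality of life and wellbeing) and costs", so psychotic symptoms are not named at that visit.

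The cost is a little more analysis work and a less precise estimate: an indirect effect combines two estimated paths, and the trial was not sized for it. A wide interval should not be read as evidence against the mechanism. No new data are needed, because the schedule of measures is not limited to one arm.

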## Discussion

Although depression is highly prevalent within individuals diagnosed with schizophrenia, there are no current evidence based interventions for the treatment of this specific co-morbid presentation. Relatively short-term structured interventions are easier to disseminate within health services, and therefore the Positive Memory Training protocol being adopted within the current trial has the potential to be both widely available and cost-effective. It is also envisaged that as the dominant focus of the intervention is on positive past experiences, that rates of patient engagement will be high.
